## Follow-Up of Adverse Events

Investigators must follow up subjects with serious adverse events until the event has stabilised or resolved, whichever is the latter. In the case of non-serious adverse events, follow-up should occur until the subject completes the study, and if possible, until the event has stabilized or resolved. Records of the subject’s progress should be maintained until the conclusion of the study and thereafter in a subject’s medical history at the relevant investigational site. Details of the subject’s progress must be submitted to the Starpharma Study Monitor on request.

## Expedited Adverse Event Reporting Requirements

This section outlines Expedited Adverse Event (EAE) reporting requirements for this study. Study sites will receive training on EAE reporting prior to the onset of study enrolment.

## Expedited Adverse Event Reporting to DAIDS and Starpharma Pty Ltd

The EAE reporting requirements and definitions for this study and the methods for expedited reporting of AEs to the DAIDS RCC Safety Office are defined in “The Manual for Expedited Reporting of Adverse Events to DAIDS” (DAIDS EAE Manual) dated May 6, 2004. The DAIDS EAE Manual is available on the RCC website: <http://rcc.tech-res-intl.com/>. The DAIDS EAE Manual is also available in the Study Procedures Manual.

AEs reported on an expedited basis must be documented on the DAIDS Expedited Adverse Event Reporting Form (EAE Reporting Form) available on the RCC website: [http://rcc.tech-res-intl.com](http://rcc.tech-res-intl.com/).

EAEs must be faxed to DAIDS and Starpharma Pty Ltd as outlined in the Study Procedures Manual. The DAIDS Medical Officer is to receive timely and synchronous communications of any AE reported to the RCC.

## EAE Reporting Requirements for this Study

EAE Reporting Level

This study uses the Intensive Level of EAE reporting as defined in the DAIDS EAE Manual.

Study Agents for Expedited Reporting to DAIDS

The study agents that must be considered in determining relationships of AEs requiring expedited reporting to DAIDS are: 3% SPL7013 Gel, applicator and INSTEAD SoftCup.

Study Agents for Expedited Reporting to Starpharma Pty Ltd

The study agents that must be considered in determining relationships of AEs requiring expedited reporting to Starpharma Pty Ltd are: 3% SPL7013 Gel.

Grading Severity of Events

The severity of adverse events will be graded according to Section 8.3.

EAE Reporting Periods

AEs must be reported on an expedited basis at the Intensive Level during the Protocol-defined EAE Reporting Period, which is:

The entire study duration for an individual participant (from study enrolment until study completion or discontinuation of the participant from study participation for any reason).

After the end of the Protocol-defined EAE Reporting Period stated above, the site must report serious, unexpected, clinical suspected adverse drug reactions if the study site staff becomes aware of the event on a passive basis, i.e., from publicly available information.

## Regulatory Reporting Requirements

Starpharma has a legal responsibility to notify both the local regulatory authority (ies) (i.e. the TGA) and other overseas agencies (i.e. the FDA) about the safety of the product/drug under clinical investigation. Prompt notification of SAEs by the Investigator is essential so that legal obligations and ethical responsibilities towards the safety of other subjects are met.

## IEC/IRB Reporting Requirements

The time frame within which the Investigators must be notified of deaths, study drug related and/or unexpected SAEs are stipulated by the local regulatory authorities.

It is the Investigator’s responsibility to comply with the requirements for IEC/IRB notification. The Investigator will notify the IEC/IRB, by promptly forwarding the Safety Report completed by Starpharma or its agent, for all onward reportable SAEs.

## Pregnancy

Study participants who become pregnant during the study period (up to and including 30 days after the last dose of investigational product) must not receive additional doses of investigational product but may continue other study procedures at the discretion of the investigator.

Study participants should be instructed to notify the Investigator if after completion of the study they become pregnant whether during the treatment phase or within 30 days following the last administration of study product.

If any female subject becomes pregnant while enrolled in the clinical study and after receipt of study product, Starpharma must be notified within 24 hours of the Investigator learning of the pregnancy. The Investigator will be asked to complete the SAE CRF without the ‘criteria of seriousness’ checked.

If the subject is in the treatment phase of the study, she will be withdrawn from the clinical study and the procedure for discontinuation of a subject will be followed (see Section 9.3).

Whenever possible, a pregnancy in subjects exposed to study product should be followed to term. Any premature terminations and the status of the mother and child after delivery should be reported to Starpharma. The Pregnancy Outcome and Questionnaire Form may be used by the Investigator to record details of the pregnancy outcome. The form includes provision to record the mothers’ status during the pregnancy, relevant medical history, and details of the health of the baby(ies) on delivery.

If a congenital anomaly/birth defect occurs, this must be reported as a SAE.

# CLINICAL MANAGEMENT

## Subject Completion

A subject will be deemed to have completed the study once all trial procedures have been conducted. Any AEs or SAEs still ongoing will be followed in accordance with Section 8.

## Subject Withdrawal

The investigator should make every reasonable effort to keep each subject in the study, except where termination or withdrawal is for safety reasons. However, if the investigator removes a subject from the study, or the subject declines further study participation, a complete exit evaluation must be performed. Should a subject decide to withdraw from the study, all efforts will be made to complete and report the reason(s) for withdrawal and observations as thoroughly as possible.

The investigator may cease study treatment and withdraw the subject, or the subject may withdraw himself from participation in the study at any time and for any reason. The following are considered justifiable reasons for subject withdrawal from the study:

- The need to take medication which may interfere with study measurements;
- Intolerable/unacceptable adverse experiences;
- Major violation or deviation of study protocol;
- Non-compliance of subject with protocol;
- Subject unwilling to proceed and/or consent is withdrawn;
- Withdrawal from the study is, in the investigator’s judgment, in the subject’s best interest;
- Other (e.g. personal reasons).

## Procedures for Handling Withdrawals

The Investigator (or delegate) must complete the reason for withdrawal and the date of withdrawal of a subject in the appropriate section of the subject’s CRF. If more than one reason applies, then the main reason for withdrawal should be indicated.

In the event that a female subject becomes pregnant at any time during the study period every attempt will be made to follow her to term (although study participant has the option to decline further follow-up), the outcome of the mother and infant documented as per Section 8.11.

## Replacement of Withdrawn Subjects

Any subjects who discontinue the clinical study of their own volition or by the investigator are defined as “drop-outs”. Drop-outs can be replaced at the discretion of the Sponsor either before or after randomisation.

.

## Loss to Follow-Up

At the start of the study the volunteer will state how they can be contacted during the study. This will be recorded in the participants' address file. If a participant fails to appear for a scheduled visit, at least three attempts to contact them should be made over the subsequent 7 days. These attempts should be documented in the participant’s study file. After these three attempts, no further efforts need be made to find them, but their file should remain open until study closeout.

If the participant does not return to the clinic before the study is closed, the CRF should be checked to indicate that the participant was lost to follow-up. The “loss to follow-up” designation cannot be made for any participant until the closing date of the study.

## Premature Termination of Study

The study may be terminated prematurely by the principal investigator or his/her designee, the sponsor, DAIDS, the FDA or TGA if:

- The number and/or severity of adverse events justify discontinuation of the study
- New data become available which raise concern about the safety of the study drug, so that continuation might cause unacceptable risks to subjects.

In addition, Starpharma reserves the right to discontinue the trial prior to inclusion of the intended number of subjects, but intends only to exercise this right for valid scientific or administrative reasons.

After such a decision, the Investigator must contact all participating subjects within two weeks, and written notification must be sent to the Ethics Committee.

# STATISTICS

## Criteria for Evaluation of Study Objectives

## Primary Endpoints

The endpoints for evaluation of primary study objectives (Primary Endpoints) are as follows:

- The total amount (mass) of SPL7013 in CV contents sampled at 0, 1, 3, 12 and 24 hours after application.
- The concentration of SPL7013 in CV contents sampled at 0, 1, 3, 12 and 24 hours after application.
- The ex vivo activity in the prevention of replication of HIV of CV contents sampled at screening and at 0, 1, 3, 12 and 24 hours after application.
- The ex vivo activity in the prevention of replication of HSV of CV contents sampled at screening and at 0, 1, 3, 12 and 24 hours after application.

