## Limitations of Study Design

It is acknowledged that CV fluid in itself has intrinsic antiviral properties, and that the amount, constituency and corresponding antiviral properties of the CV fluid will vary with the menstrual cycle. The volume and visco-elasticity of CV fluid tend to increase during the follicular development and decrease in the immediate postovulatory phase of the menstrual cycle [21].

The variation in antiviral properties is considered to be minimal in comparison with those of the active product, and therefore it is not expected to confound study results. Sampling at certain points within the menstrual cycle would lead to significant complexity within the study, and as variability is considered minimal, has not been considered necessary to build in to this study design. A baseline sample will provide an indication of the intrinsic antiviral activity of CV fluid in each woman.

The variation in volume throughout the menstrual cycle may lead to variation in the dilution of the SPL7013 samples taken throughout the study. The literature indicates a mean increase in daily CV fluid volume (SD) from 0.1 (0.01)mL on day -6 to 0.7 (0.40)mL on day -1 followed by a decrease to 0.6 (0.40)mL on day 0 [22], providing a mean variation of approximately 0.69mL. In the context of administration of a 3.5g application of SPL7013 Gel, this variation translates to an increase in percentage CV fluid in the CV fluid / SPL7013 Gel mixture in the vagina, from approximately 3% to 17%. This degree of variation is not considered significant within the context of the objective of the study which is to understand when a gross drop in SPL7013 and antiviral activity may occur, in order to provide an indication of dosing timings for future efficacy studies. At worst, the results will provide an under-estimate of activity and amount of SPL7013 remaining.

Magnetic resonance imaging techniques have demonstrated that coating of the vagina and cervix with microbicide gels reduces with time over the 24 hour period, with varying distribution [23]. It is also accepted that due to the anatomy of the vaginal vault and sampling method employed, an unknown proportion of the gel might not be accessed by the INSTEAD SoftCup. Both these factors may lead to an under-estimate of the activity and amount of SPL7013 remaining.

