In addition, It is also acknowledged that full mixing of the CV fluid and SPL7013 Gel within the vaginal vault may not occur under the circumstances of the study, however as part of the sample processing procedures, the sample retrieved using the INSTEAD SoftCup is to be vortexed, which will result in sufficient mixing of all components for antiviral testing and accurate determination of SPL7013 concentration in the sample. The concentration of SPL7013 will be used to determine the amount of SPL7013 by taking in to account the weight of the sample obtained.

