Three baseline samples will also be taken during the pre-dose period for assay validations. The same sampling method will be used except that the participants will be able to carry out this sampling at home (see Section 7.1.2.1). They will be provided with sampling kits (INSTEAD® SoftCup, centrifuge tube, sampling form, and opaque paper bag) during the screening visit and will be able to send the samples to the clinical unit by courier. As above, if any participant experiences difficulties in insertion, she may attend the clinical unit and a study Investigator may aid in the insertion or removal of the SoftCup. The three samples should be taken on different days at least 24 hours apart, and will be kept refrigerated until transportation by the courier. These samples are needed for use in validation and as standards in the activity and content assays.

The exact weight of the sample of gel plus vaginal secretions can then be calculated by subtracting the pre-recorded weight of the empty cup from the final weight of the filled cup. The centrifuge tube containing the INSTEAD® SoftCup and collected samples will be stored at 4oC and the gel processed and recovered from the tube within 24 hours.

The samples will be processed to remove the gel and samples, aliquoted and then stored frozen at -80 oC until analysis for SPL7013 concentration and activity using the assays described below.

The handling, processing, recovery and storage of CV samples is described in detail in the sample collection, processing and recovery standard operating procedures.

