## Statistical and Analytical Plan

For the primary endpoints of prevention of HIV and HSV ex vivo, the antiviral activity will be measured as a percent inhibition of replication of each virus (% inhibition) . The level of inhibition from samples taken immediately after product application (time=0) will be the Baseline reference value (100% inhibition) for each subject. The level of inhibition at all other time points will be expressed as % inhibition relative to the level of inhibition at Baseline. The comparison of mean % inhibition will be performed for each time point versus that at Baseline using an appropriate statistical test to determine if there is a statistically significant decrease in activity compared to 0 hours. If there is a statistically significant difference between the values at each time point and the 0 hour time point, comparisons may be made between the other time points.

The mass and concentration of SPL7013 in CV samples at each time point (mass is calculated from the measured concentration of SPL7013 in each CV sample) will be compared to the values immediately after application using an appropriate statistical test as outlined below. If possible (i.e. the semi-log plot of mass or concentration vs time is linear), an estimate of the half-life of SPL7013 mass and/or concentration in CV contents will be calculated.

Should the data be reasonably symmetrical and uncontaminated by outliers, a standard test such as the paired t-test will be used; if this test is compromised by outliers or an extremely non-normal distribution, then a rank-based alternative will be used. While this study has not been powered for this comparison, in the absence of any information regarding the variability of this response, this will enable an estimate to be made of the variability, so that future studies may be based on a reasonable assessment of power.

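### Section 2.3 considers only under-estimation, but the planned comparison of mass and concentration with the 0 h sample can err in either direction

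*Protocol*

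**What the plan says.** Section 10.1.1 lists as a primary endpoint "The total amount (mass) of SPL7013 in CV contents sampled at 0, 1, 3, 12 and 24 hours after application", and lists concentration at the same times beside it.

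Mass is built from what the cup brings out. Section 2.3: "The concentration of SPL7013 will be used to determine the amount of SPL7013 by taking in to account the weight of the sample obtained". Section 7.2.1: "The exact weight of the sample of gel plus vaginal secretions can then be calculated by subtracting the pre-recorded weight of the empty cup".

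Section 10.4 takes the 0 h sample as the reference for both measures: they "will be compared to the values immediately after application using an appropriate statistical test as outlined below". If the data are well behaved, "a standard test such as the paired t-test will be used", so the comparison is within woman. A half-life is to be estimated if the semi-log plot is linear.

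Each woman gives one 0 h sample, 2 to 10 minutes after dosing (Section 7). Only one sample is taken per application (Section 7.2.1), so her 0 h and later samples come from different doses and different cup insertions.

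Section 2.3 discusses error in two places:

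- On fluid volume over the menstrual cycle, it concludes: "At worst, the results will provide an under-estimate of activity and amount of SPL7013 remaining".
- On the spread of gel over 24 hours and on cup access, it accepts that "an unknown proportion of the gel might not be accessed by the INSTEAD SoftCup" and concludes: "Both these factors may lead to an under-estimate of the activity and amount of SPL7013 remaining".

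Neither place mentions error in the other direction.

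**The concern.** Gel that the cup misses, or fluid that dilutes the sample, lowers a single measurement. Read on its own, that measurement is a cautious statement of what is left. The planned analysis does not read it on its own. It sets the later value against the 0 h value, and the 0 h value carries the same kinds of error. If the error is larger at 0 h than later, the reference is pulled down further and apparent retention goes up.

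Section 2.2 says the results will support instructions on how long before intercourse the gel should be applied. A reader who takes from Section 2.3 that any error is on the cautious side would treat the observed duration as conservative. Over-stated retention is the direction that weakens that guidance, and the protocol text does not warn of it.

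**Working it through.** **Inputs.** Gel dose 3.5 g of 3% w/w (synopsis, study product). Fluid volumes 0.1 mL and 0.7 mL, and the resulting share of about 3% to 17% (Section 2.3). Time points 0, 1, 3, 12 and 24 h. The protocol gives no capture share, so every capture figure below is an assumption.

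**1. Reproduce the protocol's own figure.** Fluid share = v / (3.5 + v), taking 1 mL as 1 g.

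- 0.1 / 3.6 = 2.8%
- 0.7 / 4.2 = 16.7%

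This agrees with 3% to 17%.

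**2. Concentration against 0 h.** The gel share of the mixture is 1 − 0.028 = 0.972 on the low-fluid day and 1 − 0.167 = 0.833 on the high-fluid day. Hold the gel at 3.5 g, so that only dilution differs.

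- 0 h on the high-fluid day, later sample on the low-fluid day: 0.972 / 0.833 = 1.17
- The reverse: 0.833 / 0.972 = 0.86

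With nothing lost at all, the later sample would read 117% or 86% of 0 h. The first is an over-estimate obtained from the figures that stand beside the statement that the worst case is an under-estimate.

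**3. Mass against 0 h.** Let D be the applied dose (3.5 g x 0.03 = 105 mg), R(t) the true share remaining and c(t) the share of it that the cup captures. Recovered mass is m(t) = D x R(t) x c(t). With R(0) = 1,

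m(t) / m(0) = R(t) x c(t) / c(0).

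With true retention R = 50% at 3 h:

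| Capture at 0 h | Capture at 3 h | m(0), mg | m(3 h), mg | Ratio to 0 h | m(3 h) / 105 mg |
|---|---|---|---|---|---|
| 60% | 60% | 63 | 31.5 | 50% | 30% |
| 40% | 60% | 42 | 31.5 | 75% | 30% |
| 60% | 40% | 63 | 21 | 33% | 20% |

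Equal capture cancels. Unequal capture moves the ratio up or down. The last column stays below the true 50% in every row, because it equals R x c(t) and c(t) cannot exceed 100%.

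**4. Half-life.** Fit a straight line to log mass at the five times. The mean time is 8 h, the sum of squared deviations is 64 + 49 + 25 + 16 + 256 = 410, and the 0 h point lies 8 h below the mean. If capture at 0 h is k times the later capture, the fitted decline rate falls by 8 x ln(1/k) / 410.

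- True 3 h (rate 0.2310), k = 0.4/0.6: 0.2310 − 0.0079 = 0.2231, half-life 3.1 h. Reverse: 0.2310 + 0.0079 = 0.2389, half-life 2.9 h.
- True 12 h (rate 0.0578), k = 0.5: 0.0578 − 0.0135 = 0.0442, half-life 15.7 h.

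The effect is small when the true half-life is short and larger when it is long.

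**5. The paired test.** Simulation with 12 women, true retention 50%, independent log-normal capture with a coefficient of variation of 30% (assumed) and two-sided 5% significance. The chance of a significant decrease is 99.9% with equal mean capture, 85% when 0 h capture is 0.75 of later capture, and 2% when it is 0.5.

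**The case against.** Several points on the other side are sound.

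- **The wording is hedged.** A reader might infer that the protocol claims the capture error can only be an under-estimate. It does not. For cup access and gel distribution it says that these may lead to one. The firmer wording belongs to the paragraph on fluid volume. What stands is that under-estimation is the only direction either paragraph considers.
- **No upward bias is shown.** A reader might also infer that the design over-states retention. That needs capture at 0 h to be lower than later, and nothing in the protocol says so. Section 2.3 describes coating that falls and varies over 24 hours, but does not say how the captured share changes. If capture falls with time, retention is under-stated.
- **The half-life is fairly robust.** Using only 0 h and 3 h, the 75% ratio gives 3 ln 2 / −ln 0.75 = 7.2 h, and the 33% ratio gives 1.9 h. These are not the planned estimate. The protocol has five time points, and a fit to all of them gives about 3.1 h and 2.9 h. An anomalous 0 h point might also show on the plot.
- **The endpoint is already qualified and the limit disclosed.** It refers to contents sampled, and Section 3.1 names the SoftCup. Renaming it would be a matter of preference. The explicit rescaling of 0 h to 100% is for antiviral activity; mass and concentration are only compared with 0 h.
- **The study's aim is modest.** It looks for a gross drop, and concentration and antiviral activity are primary endpoints beside mass. Concentration does not scale with the quantity captured. It is, however, open to the dilution error in step 2.
- **Extra tables are often left to the SAP**, which is not at hand. But the choice of reference and the statement on direction are both in the protocol.

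**Conclusion.** The point holds in a limited form. Section 2.3 is right about the absolute amount remaining and incomplete for the comparison that Section 10.4 plans, which can err in either direction.

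For concentration, the protocol's own fluid shares give a factor of about 1.17 up or 0.86 down. This assumes a density of 1 g/mL and the full 3.5 g of gel in both samples. For mass, the size cannot be known, because capture in the vagina is unknown. The 98% to 103% recovery in the SoftCup section is extraction of gel from the cup and does not bound it. Under the assumed shares of 40% and 60%, a true 50% reads as 75% or 33%. The five-point half-life moves little when the true value is 3 h, and from 12 h to about 15.7 h when 0 h capture is half of later capture.

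The direction of the error is unknown. The documents do not support saying that retention will be over-stated. They also do not support treating a duration judged against 0 h as conservative.

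**What to change.** 1. In Section 2.3, keep the under-estimate statement for the absolute amount remaining. Add that comparisons with the 0 h sample can err in either direction, through capture for mass and dilution for concentration, and are not necessarily conservative.
2. In Section 10.4, report recovered mass at every time point, including 0 h, also as a percentage of the applied 105 mg (3.5 g x 3%), beside the comparison with 0 h. Tabulate recovered sample weight by time point.

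The percentage at 0 h is a check on capture: a low value in a woman warns that her comparisons with 0 h may be inflated. The percentage at later times is a lower bound on retention, provided the full dose was delivered and apart from assay and extraction error.

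The cost is one extra column, a table of weights already recorded under Section 7.2.1, and a less favourable statement about the direction of error. No new samples or assays are needed.
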